Moderately disabled ambulatory PWMS who have mobility difficulties that impact on their ability to undertake daily activities often seek outpatient or community physiotherapy with the aim of improving or maintaining mobility levels, but unfortunately, there is limited evidence to inform clinicians with regard to best practice in this area. The aim of this study, therefore, is to evaluate the effect of a possible therapeutic device (i.e. a DAO) on the six-minute walk test (6MWT), walking efficiency and perceived levels of fatigue and exertion. The 6MWT was selected as the fatiguing condition as it has been evaluated in PWMS as a measure of functional capacity and because PWMS have reduced 6MWT distance when compared with controls [14]. In addition, we anticipate that in a moderately disabled group, the 6MWT will induce fatigue and changes to gait and balance control. We will therefore examine any deterioration in function by in gait patterns, balance and tests of motor function following walking the 6MWT with and without the DAO.

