### The walking protocol and Pre- and post-walk assessments

Following initial screening and assessments, participants will be randomised with respect to condition order (i.e. 6MWT with or without DAO), and subsequently undertake the baseline pre-walk assessments. Immediately following the 6MWT, participants will undertake the post-walk assessments. The pre- and post-walk assessments include tests of strength, simple reaction time, choice stepping reaction time, standing balance, and gait analysis, as described below and presented in Figure 1. Participants will return to the laboratory within 2 weeks to complete the other 6MWT condition and associated pre- and post-walk assessments.

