#### Walking protocol & perceived exertion

Participants will wear a Polar heart rate monitor during each walking condition. Participants will be seated at rest for 2 minutes to determine a baseline heart rate. We will use a modified 6MWT version from the American Thoracic Society script with the aim of maximising effort and inducing fatigue [15]. Participants will be instructed to walk back and forth along a ten-metre walkway as fast as possible over the six-minute testing period with the instructions “walk as fast as you comfortably can, bearing in mind that you will be walking for 6 minutes”. Participants will be permitted to use assistive devices (i.e. canes) if required. Distance walked and perceived exertion will be recorded each minute using the 10-point Modified Borg Rating of Perceived Exertion (RPE) scale [16], and heart rate (beats/min) will be automatically recorded at 5-second intervals. Physiological Cost Index of walking will be calculated by the formula;

(1)$$\left(\text{average 6MWT HR }–\text{ average resting HR}\right)/\text{ walk speed}\text{,}$$

where heart rate is measured in beats/min and walk speed measured in m/min [17].

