#### Perceived fatigue levels

Participants will be asked to indicate their perceived fatigue levels will be measured using the Visual Analogue Scale for Fatigue (VAS-F) [18] immediately before and after the 6MWT.

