#### 3D Gait analysis

3D gait analysis will be conducted using an 8 camera Vicon MX3 system (Vicon, Oxford, UK) with 4 AMTI (AMTI, Watertown, MA) force plates and Helen Hayes marker set [19]. Spatiotemporal data and kinematic and kinetic data for the hip knee and ankle will be collected over a minimum of 6 walking trials with and without the DAO. Data will be collected using Vicon Nexus software (v1.4) and processed with Matlab (v7.0). Sagittal plane angles at the ankle are of particular interest, to examine effects of the DAO, in addition to knee and hip angles to identify potential compensations for DAO effects at the ankle.

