### Primary outcome measures

The primary outcome measures are walking distance, physiological cost index and perceived fatigue and exertion during the 6MWT.

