### Statistical analysis

Initially we will examine the frequency distributions, percentages and calculate means and standard deviations (mean +/−SD) for the outcome measures. Repeated measures analysis of variance (ANOVA) will be used to determine differences in the outcome measures with time and DAO condition as factors. Finally, we will examine associations between 6MWT and measures of fatigue (FSS, MFIS VAS-F & Borg RPE), EDSS scores and Postural Sway data with Pearson correlations. The data will be analysed with the Statistical Package for Social Science (SPSS) software.

We will adjust for other possible confounding variables by using a covariance analysis. Multiple regression analysis will be used to examine significant, independent predictors of 6MWT distance.

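### One time-by-condition ANOVA for every outcome does not fit PCI or total 6MWT distance, and leaves the VAS-F test unnamed and its pre-walk value unused as a covariate

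*Protocol article*

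**What the plan says.** The main analysis is a single sentence under Statistical analysis: "Repeated measures analysis of variance (ANOVA) will be used to determine differences in the outcome measures with time and DAO condition as factors". It covers the outcome measures without distinction and does not say which term tests the orthosis. A covariance analysis follows for other possible confounders, and the pre-walk value is not named among them.

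The outcomes differ in structure. Under Primary outcome measures: "The primary outcome measures are walking distance, physiological cost index and perceived fatigue and exertion during the 6MWT". Under Walking protocol & perceived exertion:

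- "Distance walked and perceived exertion will be recorded each minute using the 10-point Modified Borg Rating of Perceived Exertion (RPE) scale".
- "Physiological Cost Index of walking will be calculated by the formula", which gives one value per walk with resting heart rate already subtracted.

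VAS-F is taken "immediately before and after the 6MWT". The remaining paired measures are secondary: "The pre- and post-walk assessments include tests of strength, simple reaction time, choice stepping reaction time, standing balance, and gait analysis". Gait data "will be collected over a minimum of 6 walking trials with and without the DAO". For the other pre-walk tests the article does not say whether the orthosis is worn.

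The Background section gives the aim for the paired measures as deterioration in gait patterns, balance and "tests of motor function following walking the 6MWT with and without the DAO". Sample size calculations sizes the trial on 6MWT distance with a 2x2 cross-over test on differences.

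**The concern.** A two-factor model needs levels for both factors. PCI has none for time, and neither has distance taken as the six-minute total. For the outcome that sized the trial, the stated analysis is therefore not the cross-over comparison behind the sample size.

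For VAS-F the model can be fitted, but its terms answer different questions. The condition main effect averages the pre-walk and post-walk values. A pre-walk rating precedes the walk, so it cannot reflect an effect of walking with the orthosis, and averaging it in dilutes that effect. The interaction compares raw changes. Its estimate is undiluted, but it carries the full noise of the pre-walk value. An analysis of the post-walk value with the pre-walk value as covariate uses the same data with less noise. The stake is the chance of detecting an effect on perceived fatigue, and the size that would be reported.

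**Working it through.** **1. Structure of the four primary outcomes**

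| Outcome | Values per walk | Pre-walk value? | Possible meaning of time |
|---|---|---|---|
| 6MWT distance, total | 1 | no | none |
| 6MWT distance, per minute | 6 | no | minute of walk |
| PCI | 1 | no | none |
| Perceived exertion (RPE) | 6 | none described | minute of walk |
| VAS-F | 2 | yes | pre/post |

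**2. The plan's own figure.** The stated sample size is 35, or 40 with the dropout allowance: 35 / (1 − 0.125) = 40, where 0.125 = 5/40. No numerical SD is given, so the 35 can be neither confirmed nor refuted. At two-sided 5% and 80% power with 33 degrees of freedom, it corresponds to an SD of the paired difference of about 102, 205 or 307 m for differences of 50, 100 or 150 m. The calculation concerns distance, which has no pre-walk value, so nothing below changes the 35.

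**3. VAS-F: three ways to test the orthosis.**

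Assumptions, none from the documents:
- within-person SD 1 at each measurement;
- pre/post correlation r within a visit, after the participant effect is removed;
- orthosis effect θ = 0.6 on the post-walk value only.

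The number of participants is n = 35, from the article. Let d_pre and d_post be the with-minus-without differences. Each has variance 2, and their covariance is 2r.

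- Main effect, (d_pre + d_post)/2: estimates θ/2, variance (2 + 2 + 4r)/(4n) = (1 + r)/n.
- Interaction, d_post − d_pre: estimates θ, variance (2 + 2 − 4r)/n = 4(1 − r)/n.
- Post-walk adjusted for pre-walk: estimates θ, variance about 2(1 − r²)/n.

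At r = 0.5:
- Main effect: 0.30, variance 1.5/35 = 0.0429, SE 0.207, ratio 1.45.
- Interaction: 0.60, variance 2/35 = 0.0571, SE 0.239, ratio 2.51.
- Adjusted: 0.60, variance 1.5/35 = 0.0429, SE 0.207, ratio 2.90.

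Simulated power (5,000 replicates):

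| r | Main effect | Interaction | Adjusted |
|---|---|---|---|
| 0.3 | 33% | 54% | 71% |
| 0.5 | 29% | 68% | 79% |
| 0.7 | 27% | 89% | 92% |

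The formulas with a noncentral t distribution give the same figures to within about one and a half percentage points.

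**4. Gain over the interaction.** The variance ratio is 2(1 − r²) / [4(1 − r)] = (1 + r)/2. That is 0.65, 0.75 and 0.85 at r = 0.3, 0.5 and 0.7, or 35%, 25% and 15% less variance. The simulation at r = 0.5 gave 0.0446 against 0.0577, about 23% less, because estimating the slope costs a little.

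**5. Second check on another scale.** A separate simulation with n = 35 set the post-walk-only comparison at 80% power and the true effect at 10. Mean estimates were 4.9 to 5.0 for the main effect, 9.9 to 10.1 for the interaction and 10.0 for the adjusted model. Calculated power at r = 0.3, 0.5 and 0.7 was 41%, 37%, 33% for the main effect; 66%, 80%, 95% for the interaction; and 84%, 90%, 97% for the adjusted model. The ranking is unchanged.

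**The case against.** The strongest objection is that the article never names the main effect as the test. A two-factor repeated-measures ANOVA ordinarily contains the interaction, and the aims in the Background and Discussion, deterioration after walking and walking-induced change, point to it. This stands. A reader might infer that the plan will halve the fatigue effect; the text does not support that. Halving follows only if the main effect is read as the answer and the orthosis has no effect on the pre-walk value.

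Second, distance and RPE are logged each minute, so time can mean minute of walk and the model can then be fitted to both. This also stands, and it would be wrong to say that the ANOVA cannot be fitted to distance at all. But the word then means minutes for two outcomes and pre/post for a third, and PCI has a time level on neither reading.

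Third, for a single-value outcome the ANOVA could simply reduce to a paired comparison. That is probably what would be done, but it is not what is written, and it includes no period term.

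Fourth, a reader might extend the covariate remedy to all primary outcomes or all paired measures. Neither extension holds. Only VAS-F among the four primary outcomes has a pre-walk value. Gait is recorded with and without the orthosis; a pre-walk gait value taken with it on already carries its effect, and adjusting for that value could remove what the trial wants to see.

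Finally, preferring adjustment to the interaction is a matter of precision, since both estimate the full effect. That is true, and the gain is small when r is high.

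**Conclusion.** The point holds in limited form. The single ANOVA does not match PCI or total distance, and for distance it departs from the cross-over-differences test used for the sample size. For VAS-F the testing term is unspecified, and the pre-walk value is collected but not named as a covariate. Adjustment raises power over the interaction by about 17, 11 and 3 percentage points at r = 0.3, 0.5 and 0.7. Relying on the main effect would leave power at about 27% to 33% and halve the estimate, but that is a risk of the open wording and not something the plan commits to.

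The figures rest on the assumed 0.6 SD effect, the assumed correlations, 35 participants and no effect on the pre-walk rating. The documents give neither a correlation nor an SD, so the gain can only be shown as a range. This should be changed before analysis. It does not invalidate the design.

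**What to change.** Replace the single sentence with two models.

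1. **Total 6MWT distance and PCI:** a within-person cross-over comparison with condition, period and sequence, in line with the sample size method. If per-minute distance or RPE is to be analysed, say that time means minute of walk and name the term that tests the orthosis.
2. **VAS-F, and secondary paired measures only where the pre-walk test is done without the orthosis:** the post-walk value as response, with condition, period, sequence, that visit's pre-walk value (split into the participant mean and the within-person deviation) and a random participant effect. Name the condition coefficient as the test and report it with its confidence interval.

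State for each pre-walk test whether the orthosis is worn, and exclude from the covariates any value recorded with it on, gait in particular.

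The cost is wording and one or two degrees of freedom. No new measurement is needed.

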## Discussion

This study will examine the use of a novel ankle dorsiflexion assisting device (DAO) on walking performance in people with moderate MS and determine potential beneficial effects on walking induced changes in fatigue, gait patterns, strength, balance and reaction time. Ambulation distance has historically been a key measure of functional status and disability in PWMS [24]. A recent multidisciplinary consensus conference in 2007, with the Consortium of MS Centres in the USA, agreed that rehabilitation professionals need to improve their understanding of gait and fatigue outcome measures used in MS rehabilitation [22].

While it is known that PWMS have reduced mobility, impaired balance and higher fatigue levels compared with healthy controls, the complex interaction between these factors is not well understood. PWMS have a reduced 6MWT performance compared to healthy controls, and it is important to identify the changes in fatigue, gait, balance and motor function that result in this reduced mobility as this may identify key modifiable targets for rehabilitation. These targets may include either exercise and/or timely use of specific orthoses to maximise functional mobility while reducing the risk of falls. We believe this detailed study design will allow us to further determine what kinematic and kinetic changes are associated with prolonged walking in PWMS, providing a more detailed understanding of complex movement dysfunctions such as spasticity and localised motor fatigue. This may also help in designing individualised orthoses aimed at maximising mobility without compromising balance control. In addition we hope to deepen our knowledge of perceived fatigue and physiological performance associated with mobility.

It is likely a rehabilitation approach that uses exercises that address aspects of strength and skilled recruitment of muscles involved in walking and dynamic balance may need to be combined with individually prescribed orthoses in order to maximise mobility for PWMS. Our ability to analyse gait and balance becomes increasingly important when considering recent therapeutic advancements that have been shown to reduce clinical progression, improve disability and increase ambulation levels [25,26]. This is an important step for future research directed towards evaluating targeted interventions for improving balance and mobility and reducing fatigue in PWMS.

## Abbreviations

PWMS: People with Multiple Sclerosis; 6MWT: Six-Minute Walk Test; DAO: Dynamic Ankle Orthosis; RGH: Repatriation General Hospital; EDSS: Expanded Disability Status Scale; MS: Multiple Sclerosis; BMI: Body Mass Index; FSS: Fatigue Severity Scale; MFIS: Modifies Fatigue Impact Scale; BDI-FS: Beck Depression Inventory- Fast Scale; MSWS-12: Multiple Sclerosis Walking Scale; RPE: Rating of Perceived Exertion; VAS-F: Visual Analogue Scale for Fatigue; CSRT: Choice Stepping Reaction Time; PASS: Power Analysis and Sample Size; ANOVA: Analysis of Variance.
